### Primary outcomes

An objective evaluation of participants’ daily physical activity levels will be conducted using the Actigraph GT3X^®^ accelerometer (Actigraph LLC, USA). This physical activity monitoring tool has been validated and found to be reliable for use in individuals with COPD [47]. The level of physical activity will be assessed by measuring the amount of time spent in minutes in light, moderate, and vigorous activity categories, as well as the total time, in addition to the daily step count and indicators of energy expenditure [10]. The collected data will be processed, recorded, and stored in the device’s internal memory, generating a report that will be analyzed on a computer using the specific ActiLife 6 software (Actigraph LLC, Pensacola, FL, USA) [48].

Before commencing accelerometer use, participants received instructions on how the device functions and its purpose. An elastic strap was worn to secure the accelerometer at the line of the iliac crest of the dominant lower limb. The accelerometer was worn continuously for a period of 7 consecutive days, with removal occurring only during bathing, water-related activities, and sleep. The device’s small size and minimal dimensions ensure comfort during use. Each participant will receive the accelerometer along with a manual containing information and instructions on the proper use of the device, as well as a diary recording the day of the week and the times the device is attached and removed. After the usage period, evaluators collected the device for data analysis.

The stored data will be analyzed using ActiLife 6 software (Actigraph LLC, Pensacola, FL, USA). The data will be collected at a frequency of 30 Hz and analyzed in 60-second epochs [49]. A day of data was considered valid if there was a minimum of 10 hours of use during 24 hours (from 0:00 to 23:59) [48]. The data from the first and last days were discarded, with a minimum of four days included in the analysis; at least one weekend day was included [50, 51].

The data analysis will be limited to waking hours, excluding any records during sleep. To calculate the minutes spent on moderate and vigorous activities per week, the data from all valid days were summed, adjusted for the total number of valid days, and multiplied to obtain the individual weekly average.

The step count will also be recorded, and patients can be classified into three categories based on step count: sedentary (<5,000 steps/day), not very active (5,000–7,499 steps/day), and active (≥7,500 steps/day) [52].

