**Methods:**

The environment on physical activity for chronic obstructive disease (EPCOT) is a randomized controlled clinical trial protocol approved by our institution’s Ethics Committee and registered with The Brazilian Registry of Clinical Trials (ReBEC) (https://ensaiosclinicos.gov.br, number RBR-4tfwdhp). This protocol will involve 38 volunteers diagnosed with COPD recruited from the pulmonary physiotherapy and rehabilitation service. The volunteers were randomly divided into two walking groups: an experimental group (ERG) with guidance for walking in a suggested environment and an active control group (ACG) instructed to choose their own routes. The intervention consisted of eight consecutive weeks, with progressive walks carried out 3 to 5 times weekly. The primary outcome will be assessing participants’ physical activity levels. Secondary outcomes will include exercise capacity, quality of life, dyspnea levels, motivation, anxiety, depression, and perceptions of the environment. All assessments will occur before and after the intervention period, aiming to fill a literature gap by investigating the impact of urban environments on COPD-related physical activity. The results may shed light on the importance of environmental factors in promoting physical activity among individuals with COPD, helping to develop more effective interventions.

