### Sample size calculation

The sample size was calculated based on the primary outcome (physical activity) to detect a difference of at least 30 minutes in the weekly average physical activity between groups [33]. The analysis was conducted using G*Power 3.0.10 software (University of Kiel, Kiel, Germany) and considered the following parameters: a two-tailed test, a significance level (alpha) of 5%, and a statistical power of 90%. Based on these criteria, a minimum sample of 36 individuals was required for the study, with 16 participants per group, assuming an effect size of 1.03. To accommodate potential participant attrition and ensure the robustness of the results, an additional 20% was added to the calculated sample size. Therefore, the study will be conducted with a total sample of 44 participants.

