### Statistical analysis

All the statistical analyses were conducted using SPSS software version 22.0 (IBM Corporation, Somers, New York, USA). The normality of the data was assessed using the Shapiro–Wilk test. Variables with a normal distribution are presented as the mean and standard deviation, nonnormally distributed variables are presented as the median and interquartile range (25–75), and categorical variables are presented as the absolute and relative frequency. A significance level of 5% was used for all the statistical tests.

The data will be analyzed based on the principles of intention-to-treat, including all available data, regardless of intervention completion. Primary and secondary outcomes will be analyzed using mixed linear models [73], with analysis of ROC curve points and the minimum clinically important difference. The percentage of missing data, effect size, and other nonnormally distributed data were considered criteria for covariance structures in the mixed linear model [74, 75]. All the data will be included in the article and its supplementary materials.

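### The protocol lists at least six accelerometer measures as primary, names none as decisive, and sets 5% for every test

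*Protocol article*

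**What the plan says.** - **Abstract (Methods):** "The primary outcome will be assessing participants’ physical activity levels". No variable is named.
- **Primary outcomes:** the level of activity is to be measured by minutes across "light, moderate, and vigorous activity categories, as well as the total time, in addition to the daily step count and indicators of energy expenditure". Further down, the section describes one weekly calculation: "To calculate the minutes spent on moderate and vigorous activities per week, the data from all valid days were summed". It also adds a three-category classification by daily steps.
- **Secondary outcomes:** the list contains no accelerometer measure, so none of the above has been moved out of the primary set.
- **Sample size calculation:** "The sample size was calculated based on the primary outcome (physical activity"), for a between-group difference of at least 30 minutes in a weekly average. No intensity category is attached to those minutes.
- **Statistical analysis:** "Primary and secondary outcomes will be analyzed using mixed linear models", and "A significance level of 5% was used for all the statistical tests". The section gives no order of testing, adjustment or rule for declaring success.

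**The concern.** The trial has one headline question, whether suggested routes raise physical activity, but the article offers at least six numbers that could answer it. They can disagree. Light minutes may rise while moderate minutes do not, or steps may differ while total time does not. With every test at 5% and no variable named in advance, a reader of the results cannot tell whether the reported primary finding was fixed beforehand or was the most favourable of several.

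Two things are at stake: the type I error of the main claim, and the meaning of the power calculation, which covers a single variable that cannot be identified with certainty from the text.

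**Working it through.** **1. The plan's own figure.** The sample size section uses "a two-tailed test, a significance level (alpha) of 5%, and a statistical power of 90"%, and concludes "a minimum sample of 36 individuals was required for the study, with 16 participants per group, assuming an effect size of 1.03".
- A two-sample t test at d = 1.03, two-sided 5% and 90% power needs 20.8, so 21 per group (42 in total). The normal approximation gives 20 per group.
- Power is 80.5% with 16 per group and 85.1% with 18 per group. The stated 36 is therefore not reproduced, and 2 × 16 = 32, not 36.
- The final total does follow from 36: 36 × 1.2 = 43.2, taken up to 44, or 22 per group.

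The mismatch is a separate matter and does not affect this point. What matters here is that the calculation is for one variable at an undivided 5%.

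**2. Counting the measures.** Light, moderate, vigorous and total minutes make four, daily steps five, and energy-expenditure indicators (plural) at least six. The weekly moderate and vigorous minutes may be a seventh, or only a weekly scaling of two already counted. Six is used below.

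**3. Chance of at least one false positive among six two-sided 5% tests.**
- Independent tests: 1 − 0.95^6 = 1 − 0.735 = 0.265.
- Correlated tests: 400,000 simulated sets of six normal test statistics with common correlation r, counting sets in which any |z| exceeds 1.96. The article gives no correlations, so r is an assumption and is varied.

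| Assumed r | Any of six significant | Of which any favouring the experimental group |
|---|---|---|
| 0 (bound) | 26.5% | 14.1% |
| 0.5 | 20.7% | 10.4% |
| 0.8 | 13.9% | 7.0% |
| 0.9 | 10.9% | 5.4% |
| 0.95 | 8.9% | 4.5% |

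For a single named variable the corresponding rates are 5% and 2.5%.

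**4. A check that respects the structure.** The first row cannot occur, because total time contains light, moderate and vigorous time. A second simulation therefore used t tests with 19 per group (half of the 38 in the abstract), built total time as the sum of its parts, and tied steps and energy expenditure to total and moderate time. With assumed standard deviations, and assumed correlations between light and moderate time of 0.2, 0.4 and 0.6, the rate was 19.4%, 18.1% and 16.8%.

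**5. If all six were meant as primary.** A Bonferroni level of 0.05/6 = 0.0083 would need 31 per group for 90% power at d = 1.03. The planned 22 per group would give about 74%. The sample size was therefore not set for six adjusted primary tests.

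**The case against.** The strongest reply is that one variable was intended. The abstract and the sample size section both speak of the primary outcome in the singular. The trial is powered on a weekly average, and the Primary outcomes section gives a weekly calculation only for moderate and vigorous minutes. On this reading the longer list describes what the device yields, not six endpoints. The reading is reasonable, but the text never states it. The sample size section names no intensity. The Introduction describes the urban-circuit study cited for the 30-minute difference as showing a gain of 32.4 minutes per day, again without an intensity. Total minutes would fit the sample size section as well.

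A second reply is that no section says any one significant measure makes the trial positive, and that a separate analysis plan may control multiplicity. The first half stands: the error rates above depend on a success rule that the article does not contain. The absence of a multiplicity procedure is also not counted here as a fault. Naming the primary variable is different. It belongs in the protocol, and the article addresses it by listing several measures under the primary heading while fixing 5% for all tests.

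Blinding the analyst does not close the gap. A comparison of coded groups still shows which measures differ.

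A reader might go further and infer that the trial has six co-primary endpoints and a false-positive risk of 14–26%. The documents do not support that as a statement of fact. The range needs correlations between 0 and 0.8 as well as the unstated success rule, its upper end is unattainable, and its lower end is not a floor.

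**Conclusion.** The point holds in this form: the article does not name the accelerometer variable that decides the trial, so the type I error of its main claim is not controlled and the choice can be made after the data are seen.

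The size of the inflation is illustrative. If any one of six measures could carry the claim, the two-sided rate is about 21% at r = 0.5, 14% at 0.8 and 9–11% at 0.9–0.95, with about half of each in the experimental group's favour. It exceeds 5% throughout the range examined. If one variable was in fact fixed in advance and only that one is tested as primary, the rate is 5%, and what remains is a failure to say so.

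It would also go too far to say that the trial is powered on moderate-plus-vigorous minutes. That is plausible but not shown.

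**What to change.** Before any unblinded analysis:

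1. Name one primary variable and one time point, the post-intervention assessment after the 8 weeks. Weekly minutes of moderate-plus-vigorous activity is the natural candidate, as the only quantity for which a weekly calculation is described. State whether the two intensities are summed.
2. Have the sponsor confirm that this is the variable behind the 30-minute difference in the sample size section. If it is not, either choose the variable that is, or justify the sample size for the one chosen.
3. Align the abstract, the Sample size calculation and Primary outcomes sections, and the registry entry (not seen here) to that choice.
4. Test only that variable at 5% as primary. Move the other accelerometer measures to the secondary outcomes, with confidence intervals, as supportive evidence.

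The cost is wording and a registry update. No extra data, participants or procedures are needed. The downside is that an effect confined to another measure, such as daily steps, could no longer be claimed as a primary success.

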### Secondary outcomes

The secondary outcomes included exercise capacity, quality of life, dyspnea, anxiety and depression, exercise motivation, social participation, perceived benefits and barriers to physical activity, and environmental perception.

Exercise capacity will be assessed using the six-minute walk test (6MWT), following international guidelines for test administration [53], in a 30-meter-long corridor with a smooth surface. Participants will be instructed to walk as far as possible, as quickly as possible, without running for six minutes. Every minute, the examiner will inform the participants of the time remaining and provide standardized words of encouragement. Participants may rest if needed, but the timer will not be stopped. Two tests will be conducted with a 30-minute rest interval between them [54]. The test with the longest distance covered was used for analysis. Heart rate and pulse hemoglobin saturation (SpO2) will be continuously monitored using a portable pulse oximeter (MD Rossmax UT-100). Systemic blood pressure, dyspnea symptoms, and fatigue will also be measured before and after the test using the modified Borg Rating of Perceived Exertion scale [41]. The test may be stopped by the participant or examiner if the patient has discomfort, nausea, significant dyspnea, extreme fatigue, chest pain, or headache or if her SpO2 is <85%. At the end of the test, the distance covered was recorded in meters, and the percentage of the predicted distance reached was calculated [55]. An improvement in exercise capacity is expected, as indicated by an increase of at least 30 meters in the intervention group compared to the control group [53]. These data will be collected one week before the intervention’s start and after its completion.

Quality of life will be assessed using the Saint George’s Respiratory Questionnaire (SGRQ), which is specific for respiratory diseases and has been translated, culturally adapted, and validated for the Brazilian population [56]. The instrument addresses aspects related to three domains: symptoms, activity, and psychosocial impacts of the respiratory disease on the patient. Each domain has a maximum possible score, and the total score and domain scores range from 0 to 100. A lower score indicates a better quality of life [55]. In the context of the intervention, a significant improvement in the quality of life of the intervention group compared to the control group was expected, which may be evidenced by a 4-point reduction in the total SGRQ score [57].

Participants will report their dyspnea according to the modified Medical Research Council scale (mMRC), which has been translated, culturally adapted, and validated for the Brazilian population. This scale consists of five scores, with dyspnea grading ranging from 0 to 4, where a higher score indicates more pronounced symptoms of dyspnea [58].

Anxiety and depression will be measured using the Hospital Anxiety and Depression Scale (HADS). This scale was developed to estimate the prevalence of anxiety and depression in adults and is currently used in patients with chronic lung diseases [59]. The scale aims to identify cases (possible or probable) of anxiety and/or depression. It consists of 14 items divided into two subscales: seven questions for diagnosing anxiety disorders and another seven for diagnosing depressive disorders. Each question is scored from zero to three points (from absent to very frequent), with a maximum score of 21 points per subscale. Higher scores indicate greater severity of anxiety and depression [59]. A noticeable improvement is expected, represented by a reduction of 1.7 points in the anxiety subscale and 1.5 points in the depression subscale in the intervention group compared to the control group [60]. A clear improvement is expected, as evidenced by a reduction of 2 points in each subscale of anxiety and depression; these data were collected one week before and one week after the intervention.

The Behavioral Regulation Exercise Questionnaire (BREQ) will be used to assess patterns of self-determined behavior in physical exercise practice. It was created in 1997 [61] and was subsequently adapted in two ways. The most recent version is the BREQ-3 [62, 63], translated and adapted for the Portuguese language [63]. It consists of 23 items preceded by the following statement: "Why do you engage in physical exercise?" The respondents answered on a 5-point Likert scale indicating the degree to which they agreed that best fit their situation, ranging from "not true for me" (0) to "very true for me" (4). These 23 items are organized into six domains: motivation, external regulation, introjected regulation, identified regulation, integrated regulation (extrinsic motivation), and intrinsic regulation (intrinsic motivation). The six subscales that make up the BREQ-3 allow for the analysis of the motivation profile for physical exercise practice through the Self-Determination Index (SDI), where different weights are assigned to each subscale, with autonomous subscales receiving positive weights and less self-determined subscales receiving negative weights [64]. An improvement is expected to be detected, represented by an increase of 1 point in the autonomous subscale and a reduction of at least 1 point in the less self-determined subscale in the intervention group compared to the control group.

The Late-Life Function and Disability Instrument (LLFDI) questionnaire [65], translated and adapted for the Brazilian population [66], will be used to assess functional performance in home and community settings. This comprehensive and sensitive instrument was developed to document changes resulting from the aging process. The instrument comprises two components, disability and function, which constitute separate scales. In this study, only the disability component, which documents the frequency and limitations of individuals performing 16 activities of daily living, including basic, instrumental, and advanced activities, was used. In addition to the total scores (total frequency and total limitation), it is possible to obtain a score for each domain that comprises this scale, namely, personal role, social role, instrumental role, and management role [66]. An improvement is expected, as evidenced by a 2.4-point increase in the Z score; these data were collected one week before and one week after the intervention.

Perceived benefits and barriers to physical activity will be assessed using the EBBS-Brazil questionnaire [67], which consists of 42 items: 14 from the Barrier Scale (EBBSBAR) and 28 from the Benefits Scale (EBBSBEN). The EBBSBEN score will be calculated by summing 28 items across five domains: biological aspects, physical performance, psychological aspects, social interaction, and preventive health. The EBBSBAR score will be calculated by summing 14 items across four domains: time expenditure, physical effort, exercise environment, and family discouragement. Higher values indicate greater perceived benefits or barriers [67, 68]. An improvement is expected, as evidenced by a 2-point reduction in the score for barrier perception and a 1-point increase in the score for benefit perception. The data will be collected one week before the intervention and one week after the intervention.

Environmental perception will be assessed using the environmental perception scale for physical activity [69], which is composed of questions based on the *Neighborhood Environment Walkability Scale (NEWS)* [70, 71] and a social support scale for physical activity [72]. This version consists of 38 questions and has been validated for use with Brazilian adults [69]. This tool includes characteristics of the environment (built, natural, and social): access to commerce and places for physical activity; traffic safety; crime safety; aesthetics; neighborhood satisfaction; street and sidewalk quality; lighting; pollution; and social support for physical activity.

### Monitoring of data quality

To ensure data quality, the research assistant who collects the data sheets, also will provide feedback to the principal researcher if there is evidence that the protocol is not being followed. Data will be entered and double-checked by two people, and inconsistencies resolved by contacting the participant where appropriate or via consensus. In the event that participants discontinue or deviate from the intervention protocols, we have planned to collect specific outcome data to understand the reasons behind their decisions and assess the impact on the study results.

## Discussion

The evaluation of environmental interventions for individuals with COPD has been limited to a few rigorous studies [32–34]. This study involved a blinded, controlled clinical trial in which participants in the intervention group played an active role in selecting the most suitable walking environment. We outline the rationale and processes of a study that investigates the effectiveness of an environmental intervention involving predefined walking routes in urban areas within the neighborhood, compared to free-form walks, on physical activity and secondary outcomes, including exercise capacity, quality of life, and perceptions of dyspnea, anxiety, and depression. Additionally, we examined the barriers and benefits related to physical activity, exercise motivation, and social engagement in patients with COPD.

While moderate physical activity is highly recommended for individuals with COPD [9], symptoms, physical limitations, social barriers, and motivation often present significant challenges to adherence in this population. A personalized approach that considers environmental, social, and cultural factors to promote physical activity through tailored environmental interventions, accounting for individual differences, preferences, and needs, may enhance adherence and lead to clinical and functional benefits for individuals with COPD.

Several strengths are worth highlighting in this study protocol: i) the intervention is cost-effective and takes place in environments that reduce transportation barriers and costs by being located near the participant’s neighborhood; ii) changes in active behavior will be measured using a validated accelerometer and standardized data extraction; and iii) the protocol incorporates motivational incentive strategies for both groups by offering weekly goals for increasing walking time or the number of steps, monitored by pedometers provided to participants for eight weeks. Participants will also keep their walking and symptom diaries and receive periodic messages or calls for feedback and encouragement to continue walking. In addition, two lectures will be provided on COPD incidence information, symptom management, and the benefits of walking. Although these actions will be offered to both groups, it is possible that combining walking guidance in a favorable environment with participant preferences may result in higher levels of physical activity.

However, several potential limitations may introduce bias into the study: i) the perception of the environment, as participants become accustomed to the environment and personalized walking routes throughout the study, and their perception may change, affecting the consistency of environmental perception over time; ii) interference from external events, such as construction work or changes in the urban environment, can affect the perception of the environment during the study, introducing variability in participants’ responses; and iii) influence by the specific environment in which the intervention was carried out. Environmental conditions, such as climate, topography, and population density, can vary between different locations, limiting geographic generalization. Therefore, at the end of the study, topographical information and population density, among other characteristics in which the participants were included, were provided, allowing other researchers to evaluate the relevance of the results for different contexts.

In addition to the benefits for this clinical population, this study may offer valuable insights for public health by highlighting the role of the urban environment in promoting physical activity among COPD patients and emphasizing the importance of influencing public policies related to urban planning, transportation, and the creation of public spaces conducive to physical activity.

